## 9 Data analysis

Summary statistics for continuous variables will include N, mean, standard deviation, minimum, lower quartile, median, upper quartile, maximum. Summary statistics for discrete variables will be presented in contingency tables and will include absolute frequencies.

If not otherwise specified, p-values will be presented as two-sided p-values and two-sided confidence intervals will be displayed. All hypothesis tests will be for within group comparisons.

### 9.1 Analysis sets

#### Part A (MRA)

**Randomized set:** The randomized set will be defined as all subjects who were randomized.

**Treated set:** The treated set includes all subjects who received any amount of study treatment during the treatment period and had at least one post-baseline assessment during that period. Subjects will be analyzed according to treatment received. This will be the primary analysis set for the study.

**Per-protocol set:** The per protocol set includes all patients in the treated set who received study medication as specified in the protocol and who did not have any major protocol deviations. Subjects will be analyzed according to treatment received.

#### Part B (direct venous pressure measurement)

**Randomized set:** there is no randomization for this part of the study, so a randomized set will not be defined.

**Entered set:** The entered set will be defined as all subjects who entered the study (i.e. signed the informed consent form) and had baseline measurements made.

**Treated set:** The treated set includes all subjects who received any amount of study treatment during the treatment period and had at least one post-baseline assessment during that period. This will be the primary analysis set for the study.

**Per-protocol set:** The per protocol set includes all patients in the treated set who received study medication as specified in the protocol and who did not have any major protocol deviations.

## **9.2 Patient demographics and other baseline characteristics**

### **9.2.1 Demographics and baseline characteristics**

#### **Part A (MRA)**

Summary statistics will be presented for continuous demographic and baseline characteristic variables for each treatment group and for all subjects in the randomized set. The number and percentage of subjects in each category will be presented for categorical variables for each treatment group and all subjects.

#### **Part B (direct venous pressure measurement)**

Summary statistics will be presented for continuous demographic and baseline characteristic variables for all subjects in the entered set. The number and percentage of subjects in each category will be presented for categorical variables for all subjects.

### **9.2.2 Medical history**

#### **Part A (MRA)**

For all patients in the randomized set, any condition entered as medical history or current medical conditions at baseline will be summarized by treatment group using the system organ class and preferred term of the MedDRA dictionary. Summaries of portal hypertension and cirrhosis specific medical history and alcohol status will also be provided by treatment group for all patients in the randomized set.

#### **Part B (direct venous pressure measurement)**

For all patients in the entered set, any condition entered as medical history or current medical conditions at baseline will be summarized using the system organ class and preferred term of the MedDRA dictionary. Summaries of portal hypertension and cirrhosis specific medical history and alcohol status will also be provided for all patients in the entered set.

## **9.3 Treatments (study drug, rescue medication, other concomitant therapies, compliance)**

### **9.3.1 Study treatment**

#### **Part A (MRA)**

The analysis of study treatment data will be based on the treated set.

A summary of patients receiving the planned dose regimen of study medication and reasons for not receiving planned serelaxin dose will be presented by day and infusion period. Reason for not receiving planned terlipressin acetate bolus injection will be summarized at a single time point. For the serelaxin group, there will be two infusion periods, the first 60 minutes of infusion and the second at least 60 minutes of infusion (until the 120 min assessment procedure is completed).

## **Part B (direct venous pressure measurement)**

The analysis of study treatment data will be based on the treated set.

A summary of patients receiving the planned dose regimen of serelaxin study medication and reasons for not receiving planned serelaxin dose regimen will be presented by day and infusion period. There will be two infusion periods, the first 60 minutes of infusion and the second at least 60 minutes of infusion (until 120 min assessment procedure is completed).

### **9.3.2 Prior and concomitant treatment**

#### **Part A (MRA)**

Prior and concomitant treatments will be summarized by treatment group in separate tables.

Prior treatments are defined as treatments taken prior to first dose of study treatment. Any treatment given at least once between the day of first dose of randomized study treatment and the last day of study visit will be a concomitant treatment, including those which were started pre-baseline and continued into the treatment period.

Treatments will be presented in alphabetical order, by Anatomical Therapeutic Classification (ATC) codes and grouped by anatomical main group. Tables will also show the overall number and percentage of subjects receiving at least one treatment of a particular ATC code and at least one treatment in a particular anatomical main group.

In addition, non-drug therapies will be summarized.

#### **Part B (direct venous pressure measurement)**

Prior and concomitant treatments will be summarized in separate tables.

Prior treatments are defined as treatments taken prior to first dose of study treatment. Any treatment given at least once between the day of first dose of randomized study treatment and the last day of study visit will be a concomitant treatment, including those which were started pre-baseline and continued into the treatment period.

Treatments will be presented in alphabetical order, by Anatomical Therapeutic Classification (ATC) codes and grouped by anatomical main group. Tables will also show the overall number and percentage of subjects receiving at least one treatment of a particular ATC code and at least one treatment in a particular anatomical main group.

In addition, non-drug therapies will be summarized.

## **9.4 Analysis of the primary variable(s)**

#### **Part A (MRA)**

No statistical hypothesis tests will be performed comparing the terlipressin acetate and serelaxin groups. Only within group comparisons are performed for this study.

All efficacy analyses will be performed on the treated set.

## **Part B (direct venous pressure measurement)**

All efficacy analyses will be performed on the treated set.

### **9.4.1 Variable**

#### **Part A (MRA)**

Change from baseline of the blood flow for the total renal arteries (where the flow is the average flow over the cardiac cycle).

Total renal artery flow = left renal artery flow + right renal artery flow

#### **Part B (direct venous pressure measurement)**

Change from baseline of the portal pressure gradient

PPG = PVP-IVCP

### **9.4.2 Statistical model, hypothesis, and method of analysis**

#### **Part A (MRA)**

Summary statistics (n, mean, SD, median, quartiles, min, max, geometric mean) for the baseline, post baseline and change from baseline measurements for the blood flow parameter for patients in the serelaxin group will be presented. Confidence intervals on the change from baseline for the blood flow parameter will be calculated for both the arithmetic and geometric means.

Data analysis for the terlipressin acetate group will be analyzed in a similar manner as the serelaxin group.

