#### Part B (direct venous pressure measurement)

To investigate whether serelaxin reduces the portal pressure gradient in patients with cirrhosis, PHT and a TIPSS in situ after at least 120 min of infusion (60 min at 80 µg/kg/day and at least 60 min at 30 µg/kg/day).

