#### **Part B (direct venous pressure measurement)**

Summary statistics (n, mean, SD, median, quartiles, min, max, geometric mean) for the baseline, post baseline and change from baseline measurements for each parameter will be presented. Confidence intervals on the change from baseline for the parameters will be calculated for both the arithmetic and geometric means.

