### **Exploratory**

Change from baseline of the blood flows/flow parameters for the following blood vessels (where the flow is the average flow over the cardiac cycle):

- Total liver = average portal vein flow + average hepatic artery flow
- Hepatic artery : portal vein ratio
- Descending abdominal aorta
- Left renal artery
- Right renal artery
- Azygos vein

The secondary and exploratory efficacy parameters will be analyzed in the same manner as the primary efficacy parameter.

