## 9.6 Sample size calculation

### Part A (MRA)

This is an exploratory study. As such the study is not sized based on the power to detect a difference between treatment groups. Instead, the sample size is based on the required number of patients to identify by means of a 90% confidence interval a mean change from baseline of 25% or larger for each of the blood flow parameters. An increase of 25% is used, as this was identified as the indication of a clinically significant change in blood flow parameter that would be important to detect.

Table 9-1 contains the estimated mean and SD for each baseline blood flow parameter. The SD for the difference is estimated assuming a 10% correlation between baseline and post baseline measurements.

A sample size of 20 patients per group will be sufficient to create a 90% confidence interval on the mean change from baseline that will exclude the zero if a 25% increase is observed for that parameter, assuming the observed baseline mean and standard deviation for the study is similar to the historically observed standard deviation.

**Table 9-1** Estimated number of patients required for the 90% CI on mean change from baseline to exclude zero

| Parameter                  | Units | Mean | SD   | Estimated SD for difference | Number of patients required per group* |
|----------------------------|-------|------|------|-----------------------------|----------------------------------------|
| Total renal arteries       | L/min | 0.62 | 0.24 | 0.322                       | 14                                     |
| Hepatic artery             | L/min | 0.27 | 0.12 | 0.161                       | 18                                     |
| Superior mesenteric artery | L/min | 0.15 | 0.05 | 0.067                       | 11                                     |
| Descending thoracic aorta  | L/min | 3.32 | 0.81 | 1.087                       | 7                                      |

\*Assumes a 25% increase in mean blood flow is observed

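### The geometric mean and confidence interval that section 9.4.2 requires for the signed change from baseline cannot be computed once any change is zero or negative, which is near certain in Part A and virtually certain in Part B

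*Protocol*

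**What the plan says.** Section 9.4.1 of the protocol defines both primary variables as differences. Part A uses "Change from baseline of the blood flow for the total renal arteries (where the flow is the average flow over the cardiac cycle", and Part B uses "Change from baseline of the portal pressure gradient". No ratio or log scale is mentioned.

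Section 9.4.2 lists the geometric mean among the summary statistics for the baseline, post-baseline and change values alike. It then asks for intervals on the change. For Part A: "Confidence intervals on the change from baseline for the blood flow parameter will be calculated for both the arithmetic and geometric means". For Part B: "Confidence intervals on the change from baseline for the parameters will be calculated for both the arithmetic and geometric means". The data analysis paragraph of the synopsis repeats both. Section 9.5.2 carries the method to the other Part A variables: "The secondary and exploratory efficacy parameters will be analyzed in the same manner as the primary efficacy parameter". A matching sentence covers portal vein pressure in Part B.

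Three other places bear on this:
- The Part B primary objective (section 2.1) is directional: "To investigate whether serelaxin reduces the portal pressure gradient in patients with cirrhosis, PHT and a TIPSS in situ". The expected change is therefore negative.
- Section 9.6 sizes the study on the number of patients needed "to identify by means of a 90% confidence interval a mean change from baseline of 25% or larger". The default in section 9 is that "p-values will be presented as two-sided p-values and two-sided confidence intervals will be displayed".
- Section 9.5.6 withholds a geometric mean when zeros occur, but only for serelaxin concentrations. No such rule exists for efficacy.

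**The concern.** A geometric mean is the exponentiated mean of logs, and its confidence interval is built on the log scale. Neither exists if a value is negative, and the log of a zero does not exist either. A difference between two noisy measurements will usually have both signs across patients, even when the drug works as hoped. In Part B the position is worse: the better the drug works, the fewer positive changes remain.

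What is at stake is a stated primary output in both parts, and the same output for every secondary and exploratory efficacy variable, which the programmer cannot produce as written. Something else would have to be substituted, and the protocol does not say what.

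**Working it through.** **Inputs.** Section 9.6, Table 9-1, total renal arteries: mean 0.62, SD 0.24, SD of the difference 0.322 L/min, 20 patients per group. Table 9-2, pressure gradient: mean 9.30, SD 1.60, SD of the difference 2.147 mmHg, 6 patients. Baseline to post-baseline correlation r = 0.10. The Table 9-2 gradient is porto-atrial, whereas the endpoint uses the inferior vena cava; the table's footnote treats the two reference pressures as very similar, and I do the same.

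**Reproducing the plan's figures.** SD of the difference = SD × √(2(1 − r)): 0.24 × √1.8 = 0.322, and 1.60 × √1.8 = 2.147. The required number is the smallest n with t(0.95, n−1) × SD of the difference / √n below 25% of the mean.
- Renal flow: 25% of 0.62 is 0.155, and n = 14, as stated.
- Other vessels in Table 9-1: 18, 11 and 7, as stated.
- Pressure gradient: 25% of 9.30 is 2.325, and n = 5, as stated.

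The sizing is thus a two-sided 90% t interval on the *arithmetic* mean change.

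**Part A.** Assuming normal changes, P(change ≤ 0) = Φ(−δ / SD of the difference). At a true +25%, Φ(−0.155/0.322) = 0.315, or about 6.3 of 20 patients. P(at least one of 20) = 1 − (1 − 0.315)^20 = 99.95%.

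Sensitivity to the correlation, renal flow at a true +25%:

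| r | P(change ≤ 0) | At least one of 20 |
|---|---|---|
| 0.1 (plan) | 31.5% | 99.95% |
| 0.5 | 25.9% | 99.75% |
| 0.8 | 15.4% | 96.4% |
| 0.9 | 7.4% | 78.7% |

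Sensitivity to the effect: at +10% the chance exceeds 99.8% throughout this range of r. At +47%, the renal increase that section 1.1 reports in healthy humans, it is 98.2% at r = 0.1 but 6.4% at r = 0.9. The problem recedes only if a large effect and a high correlation occur together.

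Other vessels at +25% and r = 0.1 (non-positive share; at least one of 20): hepatic artery 33.8%, 99.97%; superior mesenteric artery 28.8%, 99.9%; thoracic aorta 22.3%, 99.3%.

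**Part B.** The sizing text speaks of a 25% increase. I use a fall of the same size, because the objective is a reduction. P(change ≤ 0) = Φ(2.325/2.147) = 0.861. P(all six positive) = 0.139^6, about 7 in a million. With no effect it is 0.5^6 = 1.6%. Even if the gradient *rose* by 25%, at least one of six would be non-positive in 59.4% of trials.

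**The case against.** The strongest reply is that the authors probably meant a geometric mean ratio to baseline, which is computable for positive flows and pressures, and that an analysis plan not shown here may say so. That may be true of the intent. But the protocol is not silent on the matter: it defines the variable as a difference and asks for the geometric mean of that difference. A later document can repair this only by departing from the protocol's words.

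It is also said that the 31.5% depends on a low planning correlation. It does, and the per-patient share falls at higher correlations. The conclusion survives at the 25% effect the plan targets.

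The reply is right that the damage is limited. The baseline and post-baseline geometric means are unaffected. So are the arithmetic mean, SD, median, quartiles and interval of the change.

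A reader might infer two stronger charges, and the document supports neither:
- *That software would drop the non-positive changes and so show a false increase.* Nothing in the protocol provides for that. Section 9.4.3 excludes only patients with missing post-baseline data, and the one rule on unusable geometric means (section 9.5.6, concentrations only) leads to non-reporting.
- *That two rival estimators let the result be picked afterwards, with a raised error rate.* Read literally, the geometric interval is missing and there is no second result to pick. A comparison of two intervals presupposes the ratio, which the text does not state. Section 9.4.2 also sets no success rule, and section 9.6 points to the arithmetic mean.

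**Conclusion.** The instruction is wrong as written. A primary output in both parts, and the same output for the secondary and exploratory efficacy variables, will almost surely be uncomputable: 99.95% of trials for renal flow in Part A at the planned effect and correlation (78.7% at r = 0.9), and all but about 7 in a million for the Part B gradient at a 25% fall. These figures rest on the protocol's planning means and SDs and on normally distributed changes.

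It does not follow that the primary analysis is lost. The arithmetic mean change and its interval stand, the sample size was derived from them and is unaffected, and the study is exploratory. A smaller gap remains: section 9.4.2 neither states the confidence level nor says that the arithmetic mean leads, although section 9.6 implies both. The point merits correction but is not critical.

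**What to change.** In section 9.4.2 and the synopsis, for both parts:
- Remove the geometric mean of the change and its interval. Replace them with the geometric mean ratio, that is, the exponentiated mean of log(post-baseline / baseline), with a 90% interval compared with 1.
- Report the ratio for a variable only if both values are positive in all patients, so not where a flow or pressure gradient is zero or reversed.
- State that the arithmetic mean change with its two-sided 90% interval, on which section 9.6 sizes the trial, is the primary estimator and that the ratio is supportive.
- Let section 9.5.2 inherit the same rule.

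The ratio suits the 25% relative target. Under an assumed lognormal model matched to mean 0.62, SD 0.24 and correlation 0.10, the SD of the log ratio is about 0.50. An observed ratio of 1.25 in 20 patients then gives a 90% interval of about 1.03 to 1.52, with 16 patients the minimum to exclude 1, so the planned group size is enough.

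The cost is wording in the protocol and analysis plan, to be settled before database lock. No new data or patients are needed.

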#### **Part B (direct venous pressure measurement)**

Summary statistics (n, mean, SD, median, quartiles, min, max, geometric mean) for the baseline, post baseline and change from baseline measurements for each parameter will be presented. Confidence intervals on the change from baseline for the parameters will be calculated for both the arithmetic and geometric means.

### **9.4.3 Handling of missing values/censoring/discontinuations**

Missing data as a result of patients not having the post baseline measurement will not be imputed. Patients with missing post baseline data will be excluded from the analysis at that time point.

### **9.4.4 Supportive analyses**

#### **Part A (MRA)**

The primary analysis will be repeated using the per-protocol set.

## **Part B (direct venous pressure measurement)**

The primary analysis will be repeated using the per-protocol set.

### **9.5 Analysis of secondary variables**

#### **9.5.1 Key secondary variables**

Not applicable.

#### **9.5.2 Efficacy variables**

### **Part A (MRA)**

Change from baseline of the blood flows for the following blood vessels (where the flow is the average flow over the cardiac cycle):

- Hepatic artery
- Superior mesenteric artery
- Descending thoracic aorta
- Portal vein

### **Exploratory**

Change from baseline of the blood flows/flow parameters for the following blood vessels (where the flow is the average flow over the cardiac cycle):

- Total liver = average portal vein flow + average hepatic artery flow
- Hepatic artery : portal vein ratio
- Descending abdominal aorta
- Left renal artery
- Right renal artery
- Azygos vein

The secondary and exploratory efficacy parameters will be analyzed in the same manner as the primary efficacy parameter.

## **Part B (direct venous pressure measurement)**

Change from baseline of the following parameter:

- Portal vein pressure (PVP)

The secondary efficacy parameter will be analyzed in the same manner as the primary efficacy parameter.

### **Exploratory**

Time from start of infusion to the beginning of the reduction in portal vein pressure.

### **9.5.3 Safety variables**

All safety evaluations will be performed on the Treated set.

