| Direct portal vein pressure measurement (part B only)                           | DS       |     | X      | X          | X              |            |                     |
| Direct right atrial and inferior vena cava pressure measurements (part B only)  | DS       |     | X      |            | X              |            |                     |
| Serious adverse events                                                                       | DS       | X   | X      | X          | X              | X          | X                   |
| Adverse events                                                                               | DS       |     | X      | X          | X              | X          | X                   |
| Study Completion form                                                                        | DS       |     |        |            |                |            | X                   |

EOS = End of study

SDD/PPW = Study drug discontinuation/Premature patient withdrawal

S = assessment to be recorded on source documentation

DS = data to be recorded on source documentation and to be entered into the database

 A complete physical examination is required at visit 1 and 3 (EOS). A short physical examination is sufficient at visit 2.

 Blood pressure will be assessed approximately every 10 min until the completion of the MRA data acquisition/direct venous pressure measurement and approximately every 15 min until completion of the 60 min recovery period.

 Women of childbearing potential only. Local urine pregnancy tests will be performed. The visit 2 test is to be performed prior to randomization and study drug administration. In case of a positive urine pregnancy result a confirmatory serum pregnancy test has to be performed at the central laboratory.

 HR will be continuously monitored via ECG from the initiation of study drug administration to end of recovery.

 Printouts of central ECG recordings should be reviewed locally in a timely manner to ensure patient safety. The 1-119 min central ECG should be performed about 60 min after initiating study drug administration.

 Only in patients receiving serelaxin study drug.

 Additional blood samples may be collected for immunogenicity and accompanying serelaxin assessments as specified in [Section 6.6.2](#).

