## **7 Safety monitoring**

### **7.1 Adverse events**

An adverse event is the appearance or worsening of any undesirable sign, symptom, or medical condition occurring after starting the study drug even if the event is not considered to be related to study drug. Study drug includes the investigational drug under evaluation and the comparator drug or placebo that is given during any phase of the study. Medical conditions/diseases present before starting study drug are only considered adverse events if they worsen after starting study drug. Abnormal laboratory values or test results constitute adverse events only if they induce clinical signs or symptoms, are considered clinically significant, or require therapy.

The occurrence of adverse events should be sought by non-directive questioning of the patient at each visit during the study. Adverse events also may be detected when they are volunteered by the patient during or between visits or through physical examination, laboratory test, or other assessments. All adverse events must be recorded on the Adverse Events eCRF with the following information:

1. the severity grade (mild, moderate, severe)
2. its relationship to the study drug(s) (suspected/not suspected)
3. its duration (start and end dates or if continuing at final exam)
4. whether it constitutes a serious adverse event (SAE)

An SAE is defined as an event which:

- is fatal or life-threatening
- results in persistent or significant disability/incapacity
- constitutes a congenital anomaly/birth defect
- requires inpatient hospitalization or prolongation of existing hospitalization, unless

hospitalization is for:

- routine treatment or monitoring of the studied indication, not associated with any deterioration in condition
  - elective or pre-planned treatment for a pre-existing condition that is unrelated to the indication under study and has not worsened since the start of study drug
  - treatment on an emergency outpatient basis for an event not fulfilling any of the definitions of a SAE given above and not resulting in hospital admission
  - social reasons and respite care in the absence of any deterioration in the patient's general condition
- is medically significant, i.e. defined as an event that jeopardizes the patient or may require medical or surgical intervention to prevent one of the outcomes listed above

All malignant neoplasms will be assessed as serious under “medically significant” if other seriousness criteria are not met.

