#### **Adverse events**

##### **Part A (MRA)**

Only treatment emergent adverse events (events started after the first dose of study treatment or events present prior to the first dose of study treatment but increased in severity based on preferred term) will be summarized.

AEs will be summarized by presenting, for each treatment group, the number and percentage of subjects having any AE, having an AE in each primary system organ class and having each individual AE (preferred term). Summaries will also be presented for AEs by severity and for study treatment related AEs. If a subject reported more than one adverse event with the same preferred term, the adverse event with the greatest severity will be presented. If a subject reported more than one adverse event within the same primary system organ class, the subject will be counted only once with the greatest severity at the system organ class level, where applicable.

Additional summaries will be provided for death, serious adverse event, other significant adverse events leading to discontinuation and adverse events leading to dose adjustment (including study treatment discontinuation).

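### The protocol's only safety population requires a post-baseline assessment as well as dosing, so a dosed patient can, in rare cases, fall outside the safety tables

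*Protocol*

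**What the plan says.** Section 9.5.3 opens with "All safety evaluations will be performed on the Treated set". Section 9.1 defines the Treated set, in the same words for Part A and Part B, as subjects who "received any amount of study treatment during the treatment period and had at least one post-baseline assessment during that period". The other sets are Randomized and Per-protocol in Part A, and Entered and Per-protocol in Part B. None of them is based on dosing alone. The Treated set is also the efficacy set; Section 9.4 says "All efficacy analyses will be performed on the treated set".

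The events to be tabulated are defined without any assessment condition. Section 7.1 takes an adverse event as one "occurring after starting the study drug even if the event is not considered to be related to study drug". Section 9.5.3 counts as treatment-emergent those "events started after the first dose of study treatment", together with earlier events that worsened. The same section also promises summaries of deaths, serious events and events leading to discontinuation.

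**The concern.** A safety table should count everyone who was exposed. Here the events are defined by exposure, but the set on which they are counted adds a second condition. A patient can therefore have an event that qualifies under Sections 7.1 and 9.5.3 and still be missing from both numerator and denominator.

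The condition does no useful work for safety. Section 9.5.3 already restricts laboratory and vital-sign changes to subjects who have both a baseline and a later value. What the condition adds is the possibility of losing a patient from the adverse event, death and discontinuation tables.

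Safety and tolerability are secondary objectives in both parts (Section 2.2). Section 3.6 says serelaxin had not been studied in cirrhosis with portal hypertension. The groups are small, so a single patient changes a percentage visibly.

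**Working it through.** The plan states no figure on this point, so the check compares the texts and then gives a scale.

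**Step 1: which set, and what it requires.** Section 9.5.3 points to the Treated set. Section 9.1 requires a dose and also that the subject "had at least one post-baseline assessment during that period". No dosing-only set is defined elsewhere in the protocol.

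**Step 2: what counts as an assessment.** The Glossary defines an assessment as any procedure that produces data the study needs. Section 6 says Table 6-1 lists all assessments. The table has rows for adverse events, serious adverse events and vital signs, each marked for 1-119 min, 120 min and recovery. On blood pressure, its footnote says: "Blood pressure will be assessed approximately every 10 min until the completion of the MRA data acquisition/direct venous pressure measurement". On this reading one blood pressure value, or the recording of the event itself, meets the condition.

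**Step 3: who can still be excluded.** Two cases remain:

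- a dosed patient who leaves within minutes, before the first reading at about 10 minutes and with nothing recorded;
- any dosed patient without the required measurement, if *assessment* in Section 9.1 is read more narrowly. At the extreme, if only the 120-minute efficacy measurement counted, the exposed window would be the whole infusion. Section 9.1 does not refer to the Glossary or rule this reading out.

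**Step 4: scale, for illustration only.** Assume one dosed patient has an event, is excluded, and no other patient has one. The protocol gives no rate for this. Inputs are 20 patients in the Part A serelaxin arm (40 randomised 1:1, Section 5.2) and 6 in Part B (Section 5.2). Section 5.5.9 replaces patients withdrawn from the study before the second MRA acquisition (Part A) or without the final portal vein and vena cava pressures (Part B).

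| Group | Replaced? | All dosed patients | Treated set as written |
|---|---|---|---|
| Part B | yes | 1/7 = 14.3% | 0/6 = 0% |
| Part B | no | 1/6 = 16.7% | 0/5 = 0% |
| Part A serelaxin | yes | 1/21 = 4.8% | 0/20 = 0% |
| Part A serelaxin | no | 1/20 = 5.0% | 0/19 = 0% |

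Exact (Clopper-Pearson) 95% intervals without replacement are 0.4% to 64.1% against 0% to 52.2% in Part B, and 0.1% to 24.9% against 0% to 17.6% in Part A. With replacement the denominator returns to its planned size, so the table alone would not show that a patient is missing.

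**Step 5: direction.** Suppose instead that the excluded patient had no event and one other patient did. Part B without replacement would then read 1/5 = 20.0% instead of 1/6 = 16.7%. The bias can go either way.

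**The case against.** The strongest reply is that the set of excluded patients is close to empty. Under the Glossary and Table 6-1, recording a reaction is itself an assessment. Patients are monitored in hospital, with blood pressure about every 10 minutes and a recovery period of at least 60 minutes. Table 16-1 labels the whole of Visit 2 as treatment, through the end of recovery. Section 5.5.9 says that stopping study drug is not withdrawal, so such a patient continues to be assessed. Serious adverse events go to the sponsor within 24 hours whatever the analysis set (Section 7.2), and other events are still recorded on the eCRF. Most of this stands and limits the point to the summary tables and to rare cases. It does not remove the mismatch: Section 9.1 still imposes a condition that the event definitions lack, and a narrower reading remains open.

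A reader might infer more than the text supports in four ways.

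- **That the condition is an efficacy requirement.** It is not. Section 9.1 does not limit the kind of assessment, and the Glossary definition is general.
- **That the rule removes the earliest and most severe reactions.** A monitored patient who reacts would normally have a blood pressure or an event recorded, and so would qualify.
- **That the bias always makes the drug look safer.** Step 5 shows it need not.
- **That replacement causes the exclusion.** Replacement applies only to patients withdrawn from the study and takes nobody out of the Treated set. It can only make a gap harder to see.

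**Conclusion.** The point holds as a minor defect of definition. The only population for safety analysis carries a condition that has no safety purpose and can exclude an exposed patient. The size is at most one or two patients in plausible cases, and most likely none. If one reactor were lost, the illustrative change is from 14.3% to 0% in Part B and from 4.8% to 0% in the Part A serelaxin arm with replacement, or from 16.7% and 5.0% to 0% without it. These figures assume a single event in a patient with no qualifying assessment; they are not a forecast. Detection and expedited reporting of serious events are not affected.

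**What to change.** Add to Section 9.1, for both parts, a Safety set: all patients who received any amount of study drug, analysed by the treatment actually received, with no assessment requirement and including patients who are later replaced. Change the opening sentence of Section 9.5.3 to refer to the Safety set. Keep the Treated set for efficacy.

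The cost is about two sentences. No extra data, visits or patients are needed, and the laboratory and vital-sign change summaries keep their own requirement for paired values.
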